### **2.0 Trial Sponsor:** None

**3.0 Role of study sponsor/funders:** Funders played no role in design and conduct of the study; collection, management, analysis, and interpretation of the data; preparation, review, or approval of the protocol or related manuscripts.

**4.0 Composition of steering committee, data management teams:** The trial team managed trial data in partnership with Health Information Technology (HealthIT) at the trial location. The ongoing review of study data by the trial team ensured that the clinical study could continue without jeopardizing participant safety and the continuing validity and scientific merit of the trial. Because the study team had developed, validated, and analyzed the precise Electronic Health Record (EHR) data needed to conduct the trial, the team led on data and safety monitoring. The PI and study coordinator were responsible for monitoring the safety of participants, and for ensuring that participants are not exposed to undue risk.

## **Study Schema**

### **1.0 Background**

Annually, 47,500 Americans die from suicide and over 800,000 die from suicide around the world. Suicide kills 132 Americans every day. The first step of suicide prevention is risk identification and prognostication prior to intervention.

Traditional suicide risk prognostication relies on clinical judgment guided by validated instruments like the Columbia Suicide Severity Rating Scale (CSSRS), and the Ask Suicide-Screening Questions toolkit. Over the last few years, multiple validated statistical models have been published to improve suicide prognostication including work by Army STARRS, REACH VET, the Mental Health Research Network, our team at Vanderbilt University Medical Center (VUMC), and more.

Recent research suggests that statistical modeling combined with face-to-face screening might be better than either alone. However, the best risk prediction model possible must be made useful through tools like clinical decision support (CDS). CDS is an approach to engaging people with technology to improve the clinical care process. For example, a clinician might receive a prompt that will improve or adjust their clinical decision-making while prescribing a medication or ordering a test. Effective CDS would prompt a better decision than standard of care: the clinician making the decision unaided.

Prior literature outside suicide research has examined forms of CDS such as interruptive (e.g., alerts) and non-interruptive (e.g., static icons or visual cues) to inform contact isolation decisions, laboratory alerts, and blood transfusions. While that research has shown interruptive CDS tends to be more effective in changing behavior, this question has not been studied via Randomized Controlled Trial (RCT) in suicide prevention to our knowledge. Also, given significant concerns around false positives in suicide screening, demonstrating adequate performance of a non-interruptive CDS would support implementing a less burdensome and stigmatizing alert.

---

### **2.0 Rationale and Specific Aims**

As above, the first step of suicide prevention is risk identification and prognostication. Researchers like our team have developed and validated predictive models that use routinely collected Electronic Health Record (EHR) data like past diagnoses and medications to predict future suicide attempt risk. Our model based in machine learning is known as the Vanderbilt Suicide Attempt and Ideation Likelihood (VSAIL). VSAIL has been validated prospectively and externally to predict suicide attempt risk with a number needed to screen (NNS) of 271 for suicide attempt and 23 for suicidal ideation. NNS is the number of people who need to receive a test result to prevent one outcome - lower NNS is better.

This study will evaluate the effectiveness of a CDS System called Vanderbilt Safecourse using VSAIL to prompt a novel Best Practice Alert (BPA) to prompt

Protocol Version #: 4

Protocol date last updated: 11/9/2023

VUMC IRB #210865

face-to-face screening with a validated suicide screening instrument like the Columbia Suicide Severity Rating Scale (CSSRS). We will compare the Interruptive BPA which includes the alert with a Storyboard icon that keeps the alert accessible if it is first "dismissed" with a Non-Interruptive Storyboard Only Prompt that does not interrupt clinicians but displays high risk predictions when present.

We seek to study if identifying patients at high predicted risk of suicide in clinical settings where suicide risk screening only happens sporadically, if at all, will include face-to-face screening rates and documentation of suicide risk assessment in their EHRs. With the Interruptive/Non-Interruptive design, we seek to test whether a non-interruptive alert is as effective in increasing face-to-face screening rates as an interruptive alert, which contributes more to "alert fatigue". If Non-Interruptive design is as effective as Interruptive, this advance would reduce potential burden of alerts in a clinical area in which risk identification might be stigmatized.

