### *Primary Hypothesis*

We hypothesize the Interruptive CDS would be more effective at prompting in-person suicide risk assessment than Non-Interruptive (20% compared to 5%). Thus, we needed at least 75 patients in each arm to achieve 90% power with 5% probability of type I error.

---

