### *Sample Size*

We hypothesize the Interruptive CDS would be more effective at prompting in-person suicide risk assessment than Non-Interruptive (20% compared to 5%). Sample size calculation indicates at least 75 patient encounters are needed in each arm to achieve 90% power with 5% probability of type I error.

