### **10.0 Statistical Considerations**

In consultation with the study biostatistician ([name]) and Learning Health System ([name]), the study team determined the following power analysis.

On average at a predicted risk threshold of 2% predicted risk (the highest risk tier in settings without universal screening), 6 patients per day are anticipated in the highest risk tier. Randomizing half to the intervention arm and half to the comparator arm and 15 patients a week per arm, we anticipate 20% of the BPA prompts will be associated with face-to-face affirmation compared to 5% in the comparator arm, which means we need 75 patients in each arm to achieve 90% power with 5% type I error, 200 total, which will require fewer than six months to accumulate. Because prior suicide attempt is rare in this cohort based on diagnostic code ascertainment, simple randomization as above is justified.

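### The specific aim asks whether the non-interruptive alert is as effective as the interruptive one, but the trial is designed and sized only to show the interruptive alert superior, so a null result could be misread as equal effectiveness

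*Protocol*

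**What the plan says.** Section 2.0 (Rationale and Specific Aims) words the aim of the two-arm comparison as a question of equal performance: "we seek to test whether a non-interruptive alert is as effective in increasing face-to-face screening rates as an interruptive alert". The next sentence attaches a practical benefit to one answer: "If Non-Interruptive design is as effective as Interruptive, this advance would reduce potential burden of alerts".

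The Primary Hypothesis, under section 2.1, is directional: "We hypothesize the Interruptive CDS would be more effective at prompting in-person suicide risk assessment than Non-Interruptive (20% compared to 5"%). Its sizing statement is that "we needed at least 75 patients in each arm to achieve 90% power with 5% probability of type I error". The Sample Size paragraph in section 6.0 repeats this, counting encounters. Section 10.0 gives the same rates and adds a different total: "we need 75 patients in each arm to achieve 90% power with 5% type I error, 200 total".

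Section 1.0 (Background) is softer than section 2.0. It says that "demonstrating adequate performance of a non-interruptive CDS would support implementing a less burdensome and stigmatizing alert", which concerns adequacy and not equality with the other arm.

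The protocol contains no non-inferiority or equivalence hypothesis, no margin and no confidence-interval criterion.

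**The concern.** The aim and the hypothesis are different questions. An 'as effective' conclusion needs evidence that any loss against the interruptive alert is smaller than some stated amount. A superiority test can show that the interruptive alert is better, but failing to show it leaves open anything from no difference to a large one.

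Because section 2.0 draws a consequence from 'as effective' and the design offers no criterion for reaching it, the nearest available result is a non-significant superiority test. Randomised patients are those in the highest predicted suicide-risk tier (section 5.0). If a null result were taken as support for the quieter alert, a substantial loss of risk assessment in that group could go unnoticed.

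**Working it through.** **Inputs from the protocol.** Rates of 20% (Interruptive) and 5% (Non-Interruptive), 5% type I error, 90% power, at least 75 per arm, 1:1 allocation. The total of 200 in section 10.0 implies 100 per arm, so both sizes are carried. Sidedness is not stated, so both are shown.

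**Inputs assumed here.** True rates of 20% and 10% (half the response lost), equal rates of 20% in both arms, and non-inferiority margins of 5, 10 and 15 points. None is in the protocol.

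**1. The plan's own figure.** Pooled two-proportion formula: n = [z(alpha)·√(2·p̄·(1−p̄)) + z(power)·√(p1(1−p1)+p2(1−p2))]² / (p1−p2)², with p̄ = 0.125.
- Two-sided 5%: n = 101 per arm. Power is 79.9% at 75 and 90.0% at 100.
- One-sided 5%: n = 82 per arm. The arcsine version gives 75.5.

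So 75 per arm fits a one-sided 5% calculation, and 100 per arm fits a two-sided one. Either way the size was chosen for a 15-point superiority difference.

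**2. How often a real loss would look null.** True rates 20% and 10%, so p̄ = 0.15, √(2·0.15·0.85) = 0.505 and √(0.16+0.09) = 0.5. Normal approximation, two-sided: power = Φ[(0.10·√n − 1.96·0.505)/0.5].
- n = 75: Φ[(0.866 − 0.990)/0.5] = Φ(−0.247) = 0.40
- n = 100: Φ[(1.000 − 0.990)/0.5] = Φ(0.02) = 0.51

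Summing the exact binomial probabilities over all outcomes of the pooled z-test gives the chance of a non-significant result:

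| Test | 75 per arm | 100 per arm |
|---|---|---|
| Two-sided 5% | 59% | 48% |
| One-sided 5% | 46% | 36% |

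Fisher's exact test, two-sided, is more conservative: power 0.32 and 0.44, so 68% and 56% non-significant. With true rates of 20% and 15%, the two-sided z-test is non-significant 87% and 84% of the time.

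**3. What the confidence interval could exclude if the arms were equal at 20%.** SE = √(2·0.20·0.80/n).
- n = 75: SE = 0.0653, 95% half-width = 1.96·0.0653 = 12.8 points
- n = 100: SE = 0.0566, 95% half-width = 11.1 points

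**4. Power to exclude a loss of size m** (one-sided 2.5%): Φ(m/SE − 1.96).
- m = 10 points: Φ(1.531 − 1.960) = 33% at 75; Φ(1.768 − 1.960) = 42% at 100
- m = 5 points: 12% and 14%
- m = 15 points, the whole design difference: 63% and 76%

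**5. Size needed for 90% power**, both arms at 20%: n = (1.960 + 1.282)²·0.32/m². This gives 337 per arm for 10 points, 1,345 for 5 points and 150 for 15 points.

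**The case against.** The strongest reply is that the operative design is consistent. The Primary Hypothesis, Sample Size and section 10.0 all state one directional question, nothing labels the trial non-inferiority or equivalence, and asking whether one alert is as effective as another can be plain language for testing a null of equality. That is fair, and it means the primary test itself is untouched. But the sentence stands under Specific Aims, says what will be tested, and is followed by a benefit that depends on equality being found.

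Three stronger readings are tempting and not supported:
- A reader might infer that the team will treat non-significance as equality. The protocol never says so; the text only leaves room for that misreading.
- A reader might infer that the Background also sets up a non-inferiority question. It speaks only of adequate performance, which can be judged from the non-interruptive arm's own rate.
- A reader might infer a planned decision to switch from one alert to the other. No such decision rule is given, and the Post-Implementation Evaluation describes the system as new to the neurology workflow, so there is no existing interruptive alert to replace.

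A statistical analysis plan that is not shown might add a margin. At a 20% rate, that would not make 75 to 100 per arm adequate for a margin of 10 points or less. The figures do depend on the assumed rate. If both arms were at 5%, 100 per arm would give 90% power for a 10-point margin, but a margin twice the rate itself would mean nothing.

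Finally, 75 is stated as a minimum, and section 10.0 expects 15 patients a week per arm. Over the six months in section 12.0 (26 weeks) that could reach 26·15 = 390 per arm, and the interval would be narrower than shown. No larger target is fixed, and a larger sample would still lack a margin.

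**Conclusion.** The point holds as a mismatch between the aim in section 2.0 and the design. The stated 'as effective' question cannot be answered by the only test that is defined and sized, and a null result could be misread as answering it.

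At the planned 75 or 100 per arm, a halving of the response from 20% to 10% would go undetected in 59% or 48% of trials with a two-sided pooled z-test, or in 46% or 36% with a one-sided one. If the arms were truly equal at 20%, a 10-point loss would be excluded in only 33% or 42% of trials. These figures rest on assumed rates and an assumed margin; the direction is the same across all the margins tried at a 20% rate.

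It should be corrected, but it does not invalidate the superiority comparison.

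**What to change.** Reword the aim in section 2.0 so that the question tested is whether the interruptive alert is superior, in line with the Primary Hypothesis. Add two statements: a non-significant result will not be interpreted as equal effectiveness, and anything said about the non-interruptive alert relative to the interruptive one will be limited to what the confidence interval for the risk difference excludes. Make the sentence on reduced alert burden conditional on that interval. The Background sentence can stay if adequate performance is tied to the non-interruptive arm's own rate with its confidence interval.

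This costs a few sentences and no patients. The trial gives up an 'as effective' claim that the planned 75 to 100 per arm could not support.

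Adding a margin without changing the size is not a good alternative, since at a 20% rate a 10-point criterion would fail more often than it succeeded even with equal arms. If the team wants to keep the aim, it needs a justified margin and a matching size: 337 per arm for 10 points under the assumptions above. At 15 a week per arm that is 337/15, or about 23 weeks. For 5 points it is 1,345/15, or about 90 weeks.

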## **2.1 Objectives**

We will measure two versions of the VSAIL-prompted CDS's effectiveness in real-world clinical settings to increase rates of face-to-face suicide risk screening. VSAIL requires only data already collected in routine clinical encounters and is calculated in real-time (seconds) at the start of a clinical visit (inpatient or outpatient) at VUMC.

### *Primary Hypothesis*

We hypothesize the Interruptive CDS would be more effective at prompting in-person suicide risk assessment than Non-Interruptive (20% compared to 5%). Thus, we needed at least 75 patients in each arm to achieve 90% power with 5% probability of type I error.

---

#### **4.0 Inclusion/Exclusion Criteria and Study Setting**

##### **Patient Inclusion Criteria**

- 1) > 18 years of age
- 2) A visit in Neurology (first phase) or other primary care setting at VUMC (second phase)

##### **Patient Exclusion Criteria**

- 1) A CSSRS conducted within one week of the visit in another care setting at VUMC

##### **Provider Inclusion criteria for post-implementation interviews**

- 1) Actively engaged with the BPA in regular patient care during the study period

##### **Provider Exclusion criteria for post-implementation interviews**

- 1) Providers who did not encounter the BPA
- 2) Providers no longer employed with VUMC

##### ***Study Setting***

The study is conducted at Vanderbilt University Medical Center (VUMC), an academic medical center in the Mid-South of the United States. Within VUMC, the trial is conducted in ambulatory Neurology clinics, a non-behavioral health setting with increased suicide risk and variable suicide prevention workflows.

The study settings in this RCT include ambulatory Neurology clinics across three divisions: Neuro-Movement Disorders; Neuromuscular Disorders; Behavioral and Cognitive Neurology

---

#### **5.0 Enrollment/Randomization**

Randomization will be done in the Epic EHR, built-in functionality. Of patients in the highest predicted risk VSAIL tier (above a 2% predicted risk [[name] et al, JAMA Open, 2021]), one half will be randomized to the Interruptive Best Practice Alert (BPA) arm (intervention) and one half to the comparator arm - the Non-Interruptive Storyboard Only Prompt. For example, in outpatient Neurology, out of 60 patient visits per day, six patients on average fall into the highest risk tier and one half of those would be randomized to have the BPA pushed to the MD/NP provider providing care that day.

Protocol Version #: 4

Protocol date last updated: 11/9/2023

VUMC IRB #210865

### *Eligibility Criteria*

All patients proceeding for routine care in the Study Settings will be eligible for the RCT during its trial period.

## **6.0 Study Procedures**

### *Prediction and Randomization*

Prediction with VSAIL occurs in real-time at the start of a regularly scheduled, routine encounter in one of the participating study clinics. The patient's registration for that visit prompts calculation of VSAIL which then populates a flowsheet in eStar. The VSAIL value above a predefined risk level (2% predicted risk based on our validation study, [name] et al, JAMA Open, 2021 above) will prompt randomization within eStar to either the intervention arm or comparator arm. The randomization occurs within eStar, the Epic EHR version at the study site, through random number generation.

### *Primary Outcome/Endpoint*

The primary outcome measured in this trial is Decision to Assess Suicide Risk, the clinician response to the intervention BPAs in each arm. This decision timepoint occurs when the practitioner interacts with the study CDS. In some instances, practitioners might "dismiss" alerts to act on them later. Each interaction including dismissals are recorded and analyzed to understand behavior around this study CDS.

### *Secondary Outcomes/Endpoints*

Secondary trial outcomes include rates of thirty-day episodes of suicidal ideation, suicide attempt, rates of documented suicide risk assessment in clinical notes, psychiatric hospitalization, or emergency department utilization related to mental illness and/or suicide risk.

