**Figure 2: Storyboard icon (Passive Arm and "dismissed" BPA view)**

Patients will experience routine care until providers screen for suicidality which they might not otherwise do without the VSAIL-prompted BPA for those identified at highest risk. That screening will take the form of the validated CSSRS or provider-chosen alternative (e.g., Patient Health Questionnaire-9 or direct questions about suicidal thinking posed by providers in their own way, the latter is consistent with known best practices to screen for suicidality in a direct and caring way; best practices do not dictate a single accepted screening instrument).

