### *Participant Timeline*

Randomization, interventions, and assessments all occur within each study encounter with no follow-up or additional interventions for either study participants (practitioners) or patients.

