#### *Auditing*

Study data will be analyzed by the PI and study team every three months for 1) continued validity of VSAIL to predict suicide attempt; 2) proper functioning of the VSAIL model [e.g., ensuring all predictors continue to be calculated appropriately for patients]; 3) rates of suicidal ideation and suicide attempt in patients randomized in the study. Because this study necessitates close collaboration with providers receiving BPAs, the study team will have monthly small-group meetings with providers in study sites at VUMC to assess for problems or perceived AEs related to the study protocol, though none are anticipated.

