## **12.0 Follow-up and Record Retention**

The study will last six months.

As per IRB policy VI.B, all study data will be maintained for six (6) years from the date of the last use of study Protected Health Information (PHI) - at the conclusion of the trial period to identify patients in need of outcome data collection (which is based in EHR queries only).

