*Informed Consent – Post-trial qualitative evaluation*

For those providers who choose to participate, we will email each participant the link to RedCap eConsent form in advance of the interview. The RedCap eConsent framework allows participants the ability to download a copy of their signed consent form. At the start of the interview session, we will review the elements of the informed consent and give participants an opportunity to ask questions of the researcher. During this consent conversation, providers will be reminded that participation is optional and that they may choose to withdraw at any time without any consequences.

*Confidentiality*

Data will be collected from the EHR and stored securely in the VUMC Data Center on servers owned by the study team for later analysis. These systems are designed to securely store Protected Health Information and include encrypted storage, multifactor authentication, and both physical (locked doors, secure facility) and technical (active directory user authentication) controls. Protected Health Information, while necessary to conduct study analyses, will never be exported from these servers or shared.

Data to be collected include the VSAIL-produced probability, the predictors for that probability including historical counts of diagnoses, demographics (age, sex, race, zip code), medication counts, visit utilization (counts of outpatient, inpatient and emergency department visits) for the preceding five years. We will also collect documented and coded suicidality including suicidal ideation (a single

ICD10 code) and suicide attempt (a reference set of ICD10 codes used by our team and others from the CDC Center for National Health Statistics). We will also collect decision support usage statistics included face-to-face screening rates (the Columbia SSRS), and responses to the BPA: 1) "intent to screen" based on the alert; 2) "already screened for suicidality in this visit"; 3) "I disagree with this alert". Additional data will be collected from the same EHR data to evaluate secondary outcome and process metrics following the randomization: emergency department utilization; psychiatric consultation; documentation of suicide screening in clinical notes.

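### Thirty-day suicidal ideation is counted from routine coding that the alert itself is meant to increase, so the arm comparison mixes detection with outcome; the timeline's denial of follow-up also needs reconciling

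*Protocol*

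**What the plan says.** Protocol section 6.0, Secondary Outcomes/Endpoints: "Secondary trial outcomes include rates of thirty-day episodes of suicidal ideation, suicide attempt", followed by documented risk assessment, psychiatric hospitalization and related emergency department use. It gives no direction of benefit and does not say whether ideation found at the randomized visit counts.

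The data source is in section 13.0, Confidentiality: "documented and coded suicidality including suicidal ideation", identified by one ICD10 code. The same section anchors the secondary data in time: "Additional data will be collected from the same EHR data to evaluate secondary outcome and process metrics following the randomization". Randomization takes place at check-in (section 6.0, Prediction and Randomization; Recruitment), before any clinician could have asked.

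The intervention is meant to change who is asked. Section 6.0, in the text at Figure 2, says that care is routine until "providers screen for suicidality which they might not otherwise do without the VSAIL-prompted BPA". The Sample Size paragraph puts the expected rates of in-person assessment at 20% and 5%.

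Section 8.0, Auditing, has the study team review, every three months, "rates of suicidal ideation and suicide attempt in patients randomized in the study".

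Section 6.0, Participant Timeline, states: "Randomization, interventions, and assessments all occur within each study encounter with no follow-up or additional interventions for either study participants (practitioners) or patients". Section 12.0, by contrast, speaks of using records at the end of the trial period "to identify patients in need of outcome data collection (which is based in EHR queries only").

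**The concern.** A coded diagnosis of ideation requires that someone asked or was told, and that someone coded it. The trial tests a device that makes asking more likely in one arm. Ideation uncovered because of the alert falls after randomization and inside any thirty-day window anchored there, so nothing in the protocol keeps it out of the secondary outcome. The between-arm rate would then combine two different things: what the alert uncovered at the visit, and what happened to the patient afterwards. A reader could take the first for the second and report more ideation under the interruptive alert as a worse clinical result.

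The timeline wording is a second, smaller problem. If all assessments end with the encounter, a thirty-day outcome has no place in the schedule. The two statements cannot both stand as written.

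**Working it through.** **The plan's own figures.** The protocol gives no expected rate for thirty-day ideation, so there is nothing to reproduce for this outcome. Its 75 per arm concerns the primary outcome; the pooled normal formula at two-sided 5% and 90% power gives 101, but that is a separate matter and does not enter here. Expected counts below use 100 per arm (half of the 200 total in section 10.0).

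**Inputs.**
- s, probability of assessment: 0.20 interruptive, 0.05 non-interruptive (section 6.0, Sample Size).
- c, probability that assessing a patient with ideation produces the code: assumed 0.5 to 1.0.
- b, probability that ideation not picked up that way is coded anyway: assumed 0 to 0.2, equal in both arms.
- π, true ideation rate, identical in both arms: assumed 4.3% to 30%. The low end is 1/23, from the number needed to screen for ideation in section 2.0. That section defines the figure as people tested to prevent one outcome, so reading it as a prevalence is itself an assumption.

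**Formula.** Recorded rate = π × [s·c + (1 − s·c)·b]. The ratio between arms does not depend on π.

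| c | b | Interruptive, as share of π | Non-interruptive, as share of π | Ratio |
|---|---|---|---|---|
| 1.0 | 0 | 0.200 | 0.050 | 4.00 |
| 1.0 | 0.1 | 0.200 + 0.80 × 0.1 = 0.280 | 0.050 + 0.95 × 0.1 = 0.145 | 1.93 |
| 1.0 | 0.2 | 0.360 | 0.240 | 1.50 |
| 0.5 | 0 | 0.100 | 0.025 | 4.00 |
| 0.5 | 0.1 | 0.190 | 0.1225 | 1.55 |
| 0.5 | 0.2 | 0.280 | 0.220 | 1.27 |

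**Absolute excess** = π × 0.15 × c × (1 − b). Smallest: (1/23) × 0.15 × 0.5 × 0.8 = 0.26 percentage points. Largest: 0.30 × 0.15 × 1 × 1 = 4.5 points.

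**Expected recorded cases per 100 patients, interruptive against non-interruptive.**
- π = 1/23, c = 1, b = 0: 0.87 against 0.22.
- π = 10%, c = 1, b = 0.1: 2.8 against 1.45.
- π = 30%, c = 1, b = 0: 6.0 against 1.5.

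Over the whole grid, the chance of a nominally significant difference at 100 per arm is about 4% to 39% (normal approximation, rough with so few events).

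**What a split at the index encounter achieves.** Let r be the probability that a patient coded at the index visit is coded again within thirty days. The later count is π × [s·c·r + (1 − s·c)·b]. If r = b, the arms are equal. If r = 0 (and b > 0), the ratio is (1 − 0.20c)/(1 − 0.05c): 0.80/0.95 = 0.84 for c = 1 and 0.90/0.975 = 0.92 for c = 0.5. If r = 1, the expression returns to the table above. The split therefore separates the detection component, but the later count is free of detection bias only in the special case r = b.

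**The case against.** **Follow-up exists.** A reader might infer from the Participant Timeline that thirty-day events cannot be counted. Sections 12.0 and 13.0 do not support that: both provide for outcome data drawn from the EHR after randomization. The timeline sentence most naturally means no study visits or contacts. This objection stands; what remains is a contradiction in wording.

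**Truncated windows.** One might also infer that patients randomized late will have incomplete windows. That would follow only if data were extracted when enrolment ends, which the protocol does not say. On that assumption, section 10.0's 15 per week per arm gives 200/30 = 6.7 weeks of enrolment, and the last 30/7 = 4.3 weeks (about 129 patients) would be affected; with even enrolment over six months it would be about one sixth. The risk is conditional, but one sentence prevents it.

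**The audit.** It is tempting to say that the audit will raise a false safety signal. Section 8.0 states no comparison by arm, no threshold and no decision rule. If rates are pooled, detection raises the overall level without creating a contrast between arms.

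**Four-fold is the extreme.** It requires that no ideation be coded except through the prompted assessment. The 20% and 5% also refer to the clinician's decision in response to the alert, which may include a stated intention to screen, and informal questioning is permitted. Completed, coded screens may be fewer. Hence the range, and hence the conditional wording.

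**SAP detail.** Window start and extraction date are often left to the SAP, which was not available for this review, so their absence is not itself the fault. The protocol does, however, fix the outcome, its source and a timeline that contradicts it.

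**Conclusion.** The point holds in conditional form. If the interruptive alert produces the hypothesized gap in assessment, and assessments lead to codes, recorded thirty-day ideation is expected to be about 1.3 to 4.0 times as high in the interruptive arm with identical true ideation, an excess of 0.26 to 4.5 percentage points. The 20% and 5% are the protocol's; π, c and b are assumptions. The expected direction is the same across the assumed range, but it does not follow that the trial will observe more ideation in that arm: at the low end of π with c = 1 and b = 0, both arms expect fewer than one case per 100. Small counts make the bias hard to see without making the comparison interpretable.

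A between-arm difference in coded ideation therefore cannot be read as harm or benefit without separating index-visit detection. The primary outcome is not affected. The timeline statement needs reconciling with the thirty-day outcome and with the planned EHR queries.

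**What to change.** 1. Report ideation first coded at the index encounter separately, by arm, as detection yield.
2. Count thirty-day ideation and suicide attempt after the index encounter ends.
3. Keep psychiatric hospitalization and emergency department use counted from randomization, so that admissions or transfers directly from the visit are not lost.
4. State that later coded ideation, and service use, can still be affected by screening, and say whether a patient already coded at the index visit can count again.
5. If the section 8.0 audit looks at ideation by arm, read it with the same split.
6. Reword the Participant Timeline: no study visits or contacts, but 30 days of passive EHR follow-up after each randomized encounter, with data extracted at least 30 days after the last one.

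If the SAP already sets the window and the extraction date this way, only the protocol wording needs to change.

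The cost is a date rule in the EHR query, a few sentences of text and a wait of up to 30 days before final extraction. The downsides are fewer counted ideation events, in a trial that already expects few, and a residual detection bias that the split reduces but does not remove.
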